## Abstract

**Background:**

The initial treatment of acute necrotizing pancreatitis is conservative. Intervention is indicated in patients with (suspected) infected necrotizing pancreatitis. In the Netherlands, the standard intervention is necrosectomy by laparotomy followed by continuous postoperative lavage (CPL). In recent years several minimally invasive strategies have been introduced. So far, these strategies have never been compared in a randomised controlled trial. The PANTER study (PAncreatitis, Necrosectomy versus sTEp up appRoach) was conceived to yield the evidence needed for a considered policy decision.

**Methods/design:**

88 patients with (suspected) infected necrotizing pancreatitis will be randomly allocated to either group A) minimally invasive 'step-up approach' starting with drainage followed, if necessary, by videoscopic assisted retroperitoneal debridement (VARD) or group B) maximal necrosectomy by laparotomy. Both procedures are followed by CPL. Patients will be recruited from 20 hospitals, including all Dutch university medical centres, over a 3-year period. The primary endpoint is the proportion of patients suffering from postoperative major morbidity and mortality. Secondary endpoints are complications, new onset sepsis, length of hospital and intensive care stay, quality of life and total (direct and indirect) costs. To demonstrate that the 'step-up approach' can reduce the major morbidity and mortality rate from 45 to 16%, with 80% power at 5% alpha, a total sample size of 88 patients was calculated.

**Discussion:**

The PANTER-study is a randomised controlled trial that will provide evidence on the merits of a minimally invasive 'step-up approach' in patients with (suspected) infected necrotizing pancreatitis.

## Background

The initial treatment of acute necrotizing pancreatitis is conservative [1-4]. Once (peri-)pancreatic necrosis becomes infected mortality increases steeply [3,4]. Intervention is indicated when infection of (peri-)pancreatic necrosis is proven by fine needle aspiration (FNA), when (peri-)pancreatic air collections in the necrotic cavity are depicted on computer tomography (CT) scan or when sepsis persists despite maximal support on the intensive care unit. Surgical intervention within the first 14 days after the onset of symptoms should be averted because of notoriously poor outcome in this phase of disease [4,5]. Organ failure needing intensive care treatment during the first two weeks should be interpreted as a complication of a systemic inflammatory response syndrome (SIRS).

There is no consensus in the literature on the optimal surgical strategy in infected necrotizing pancreatitis. In a recent systematic review we demonstrated that necrosectomy by laparotomy was accompanied by high mortality rates (15–27%) and considerable morbidity [6].

In recent years radiologists, gastrointestinal surgeons and gastroenterologists have adopted minimally invasive strategies in infected necrotizing pancreatitis [7]. Initially only practiced in patients unfit for laparotomy, but in recent years indications seem to have expanded [8-11]. Percutaneous catheter drainage (PCD)  [12-14]. endoscopic transgastric procedures [15,16]. and minimally invasive necrosectomy [9-11]. have been proposed as alternatives for necrosectomy by laparotomy. Although preliminary results are promising, current series are small, poorly comparable and a selection bias may have influenced the results [7].

It has been reported that PCD obviates the need for surgical intervention in infected necrotizing pancreatitis in 30 to 100 per cent of cases  [12-14]. In these series committed radiologists repeatedly performed repeated drainage procedures using large bore catheters. It has been argued that because of the need for repeated procedures PCD can not easily be implemented in clinical practice [17]. However, we hypothesize that 'simple' drainage with regular bore (12–14 French) percutaneous catheters can also be beneficial to the patient. Drainage of 'infected fluid under pressure' may help the patient in dealing with the (peri-)pancreatic necrosis and delay or even obviate surgical intervention in a relevant proportion of patients.

As a prelude to the present study a retrospective multicenter study was performed in 11 hospitals in the Netherlands [8]. The outcome of the different interventional strategies in (infected) necrotizing pancreatitis was assessed. The strategy most often used was laparotomy with continuous postoperative lavage (CPL) (53/106 patients) [8]. Of the patients treated with minimally invasive surgery (n = 18), two-thirds had PCD prior to surgical intervention. During surgery the percutaneous drain was used as a 'guide wire' to facilitate retroperitoneal access to the infected collections. The results of minimally invasive surgery were favourable: 11% mortality as compared to 25% after laparotomy and CPL. However, since selection bias may have played a role in the favourable results a randomised controlled trial is warranted in order to define evidence-based surgery in infected necrotizing pancreatitis.

We anticipate that a minimally invasive 'step-up approach' results in a reduction in postoperative major morbidity and mortality. The PANTER trial is designed to compare a minimally invasive 'step-up approach'with a primary maximal necrosectomyby laparotomy. The 'step-up approach' consists of percutaneous or transgastric drainage when necessary followed by minimally invasive necrosectomy.

## Methods/design

### Study objectives

To test the hypothesis that a minimally invasive 'step-up approach' will lead to a reduction of postoperative major morbidity and mortality in patients with infected (peri-)pancreatic necrosis.

### Primary endpoint

The primary endpoint is the proportion of patients with major morbidity or mortality, see Tables 1 and 2. Complications occurring subsequent to the first intervention after randomisation until three months after discharge from the hospital are compared.

### Secondary endpoints

Secondary endpoints are 'minor' complications (such as pancreatic fistula, pancreatic pseudocyst requiring intervention, pancreatic abscess, biliary strictures, incisional hernia requiring re-intervention and pancreatic insufficiency), new onset sepsis, new onset SIRS, total number of interventions, hospital and intensive care stay, quality of life and total (direct and indirect) costs.

### Definitions

The definitions of the Atlanta classification are used. *Pancreatic necrosis*: focal area's of non-enhancing pancreatic parenchyma on contrast-enhanced computer tomography (CECT). *Infected necrotizing pancreatitis*: a positive culture of pancreatic or peripancreatic necrosis obtained by FNA or the presence of air in the collections on CECT. *Suspected infected necrotizing pancreatitis*: persisting sepsis or progressive clinical deterioration despite maximal support on the intensive care unit in case of pancreatic and/or peripancreatic necrosis.

### Design of study

PANTER is a randomised controlled parallel group superiority multicenter trial.

### Participating centres

Twenty hospitals of the Dutch Acute Pancreatitis Study Group, including all Dutch university medical centres, will enrol patients (see Appendix).

### Pre-randomisation treatment protocol

All patients with acute pancreatitis will be treated by a pre-established treatment protocol consisting of enteral nutrition via a nasojejunal tube and an early endoscopic retrograde cholangiopancreatography (ERCP) with sphincterotomy in case of predicted severe biliary pancreatitis with or without obstructive cholangitis. No antibiotic prophylaxis will be administered. CECT will be performed in patients who fail to show clinical improvement after the first 7 days of hospital admission. Since many patients are referred from other centres, violation of the pre-randomisation treatment protocol is not an exclusion criteria.

#### Registration

From all patients with (peri-)pancreatic necrosis, including those who are not randomised and treated conservatively, written informed consent will be obtained for prospective registration of age, gender, onset of symptoms, interventional procedures, hospital stay, intensive care stay and mortality (alternatively consent by proxy will be obtained for patients who are unable to give consent eg. intubated patients).

#### Timing of intervention

Whenever possible it is attempted to delay surgical intervention. Ideally, the first intervention would be performed at least 30 days after onset of symptoms. Earlier intervention may be warranted in case of a rapidly deteriorating clinical condition. When infection is proven within the first 14 days, intervention may be postponed. Intervention within 14 days is only indicated in emergencies such as bowel perforation, abdominal compartment syndrome or acute bleeding. Patients with these complications are not eligible for randomisation.

### Eligibility criteria

#### Inclusion criteria

▪ age equal to or above 18 years

▪ pancreatic necrosis or peripancreatic necrosis detected on CECT.

▪ patients in whom a decision for surgical intervention has been made because of (suspected) infected (peri-)pancreatic necrosis

▪ possibility of placing a drain (either percutaneous or endoscopic) in the collection(s)

▪ written informed consent

#### Exclusion criteria

▪ previous drainage or surgical necrosectomy for (suspected) infected pancreatic necrosis, including procedures performed in referring hospitals. ERCP with or without papillotomy is allowed.

▪ previous exploratory laparotomy for acute abdomen and diagnosis of pancreatitis during laparotomy

▪ acute flare-up of chronic pancreatitis

▪ bleeding, abdominal compartment syndrome or perforation of a visceral organ as indication for intervention

▪ post-abdominal surgery necrotizing pancreatitis

Rationale: previous drainage procedures or laparotomy make it impossible to study the isolated effect of drainage of 'infected fluid under pressure'. There is essentially no indication for necrosectomy in acute fluid collections, pancreatic abscesses or pseudocysts as these collections do not contain pancreatic necrosis or necrotic debris according to the Atlanta Classification. When intervention is indicated in these types of collections this is performed by drainage procedures, although some pseudocysts may require surgical intervention [4]. Patients with chronic pancreatitis have an underlying disease with a course very different from acute pancreatitis. Patients with a second, third or fourth attack of acute pancreatitis are eligible for randomisation as long as there are no signs of chronic pancreatitis (calcification and/or pancreatic duct abnormalities).

### Randomisation

Patients will be randomly assigned to group A ('step-up approach') or group B (laparotomy) as shown in the flowchart (see figure 1). Randomisation is performed by an Internet randomisation module (Julius Center for primary care and health sciences, UMC Utrecht, the Netherlands). Block-randomisation is used and the randomisation is stratified according to the (im-)possibility of placing a percutaneous drain through the (preferably left) retroperitoneum, since this step is essential to perform minimally invasive necrosectomy.

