#### Sample size and sequential interim-analysis

Sequential analysis is used to determine the difference in treatment effect on the primary endpoint (see Methods/design section), therefore no fixed sample size estimate can be given [18]. Based on the results of the Dutch retrospective multicentre audit (mortality 25% versus 11%) and PCD results from the literature is anticipated that the minimally invasive 'step-up approach' will reduce the occurrence of the primary endpoint from 45% to 16%. The expected reduction of mortality and morbidity are 10% and 19% respectively. With 80% power at 5% alpha (two-sided) complete data from about 52–77 patients will be necessary to demonstrate this effect, if it truly exists. If no such effect appears, the trial will continue until 88 patients are randomised and available for analysis as 'conventional' sample size calculation with 80% power at 5% alpha (two-sided) would require 88 patients.

Descriptive methods will be used to assess the quality of the data, comparability of treatment groups and endpoints. Continuous sequential analysis will be performed with PEST (PEST 4: user manual. MPS Research Unit (2000), the University of Reading) according to the restricted procedure as described by Whitehead [18]. Every time an endpoint occurs, data management will send a blinded, updated dataset of all included patients to the biostatistician. If one of the boundaries of the sequential analysis plot is crossed during the analysis of the cumulative data, i.e. the difference in treatment is of at least the expected magnitude, the trial steering committee will be informed and will be advised to stop randomising new patients for the trial. The trial steering committee will not be advised to stop early when no relevant differences between the treatments are observed. Next to the primary analysis, the outcome of both groups will also be adjusted forimbalance in presence of preoperative (multi-) organ failure and timing of intervention (after 28 days). These factors, including possibility of performing VARD and the individual components of the primary endpoint will also be included in a multivariate and subgroupanalysis.

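### Allocation is stratified by retroperitoneal drain feasibility, but the primary sequential analysis as described names no stratum; summing the statistic over strata is a minor, nearly free improvement

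*Protocol article*

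**What the plan says.** The protocol article names one stratification factor for the blocked allocation: "the randomisation is stratified according to the (im-)possibility of placing a percutaneous drain through the (preferably left) retroperitoneum". The reason given is practical: "since this step is essential to perform minimally invasive necrosectomy".

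Under the heading on sample size and sequential interim-analysis, the primary comparison is set out as follows: "Sequential analysis is used to determine the difference in treatment effect on the primary endpoint". PEST is used with the restricted procedure, and the data are re-analysed each time an endpoint occurs. No stratum or covariate is mentioned for this analysis. Alongside it, the outcome is also to be adjusted for imbalance in two other variables, preoperative organ failure and timing of intervention. A factor related to the stratum appears one sentence later: "These factors, including possibility of performing VARD and the individual components of the primary endpoint will also be included in a multivariate and subgroupanalysis".

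**The concern.** The factor that governs allocation is absent from the described primary analysis and from the list of adjustment variables, although that list shows that covariates were considered. Because the adjusted analysis is presented as an addition to the primary one, the natural reading is that the primary analysis is unadjusted and unstratified.

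Stratified allocation removes chance imbalance between arms in the stratum. If the stratum predicts the outcome, the difference between arms then varies less than an unstratified variance assumes. The test rejects too seldom under the null and gives up some power. Events are few: at 44 per arm (1:1 assumed) and the planned risks, 44 × 0.45 + 44 × 0.16 = 19.8 + 7.0, or about 27.

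There is a plausible route for the stratum to matter. Under Step two, a group A patient in whom VARD is not technically feasible has the group B operation instead.

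**Working it through.** **Inputs from the protocol article.** The planned effect is that the step-up approach "will reduce the occurrence of the primary endpoint from 45% to 16" per cent, with 80% power at two-sided 5% alpha and a maximum of 88 patients. The allocation ratio is not stated, so 1:1 is assumed.

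**Inputs not in the article, so assumed.** The share of patients in each stratum (the Discussion says only that VARD is possible in most patients), the odds ratio between strata, and a block size of 4. Splits from 50/50 to 90/10 and odds ratios from 1 to 10 were tried, with the smaller stratum at higher risk.

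**Step 1. Reproduce the plan's figure.** The pooled risk is (0.45 + 0.16)/2 = 0.305 and the difference is 0.29.

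n per arm = [1.960 × √(2 × 0.305 × 0.695) + 0.842 × √(0.45 × 0.55 + 0.16 × 0.84)]² / 0.29² = 38.4, so 39 per arm and 78 in total.

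With the continuity correction this becomes 45 per arm, 90 in total, within two patients of the stated 88. Without the correction, power at 44 per arm is 85.3%.

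**Step 2. Why the unstratified test is conservative.** Under the null, with overall risk p and stratum risks p_s, the ratio of the true variance to the variance used is

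r = 1 − Var(p_s) / [p(1 − p)], and the true size is 2[1 − Φ(1.96/√r)].

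Example: p = 0.305, split 70/30, odds ratio 3. The stratum risks are 0.232 and 0.475. Var(p_s) = 0.7 × 0.073² + 0.3 × 0.170² = 0.0124; p(1 − p) = 0.212; r = 0.941; true size about 4.3%. At an odds ratio of 1, r = 1 and nothing is lost.

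**Step 3. Simulation, fixed test at 88 patients.** The two tests are the score test on the pooled 2 × 2 table and the stratified score test, with sums over strata s:

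Z = Σ (x_As − m_s n_As/n_s), V = Σ n_As n_Bs m_s(n_s − m_s) / [n_s²(n_s − 1)].

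Here x_As is the number of events in group A, m_s all events, n_As and n_Bs the arm sizes and n_s the stratum size. There were 400,000 runs per setting. Marginal risks were held at 45% and 16% for power, and at 45% in both arms for size. Ranges run over splits of 50/50, 70/30, 80/20 and 90/10.

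| Stratum odds ratio | Power, unstratified | Power, stratified | Gain (points) | Size, unstratified | Size, stratified |
|---|---|---|---|---|---|
| 1 | 85.7–85.8% | 85.8% | 0 | 4.4% | 4.5–4.6% |
| 2 | 85.9–86.1% | 86.1–86.6% | 0.2–0.5 | 4.2–4.4% | 4.7–4.8% |
| 3 | 86.0–86.4% | 86.6–87.6% | 0.6–1.2 | 3.7–4.2% | 4.9–5.0% |
| 5 | 86.4–87.1% | 87.6–89.5% | 1.2–2.5 | 3.0–4.0% | 4.9–5.0% |
| 10 | 87.0–88.2% | 89.4–92.7% | 2.4–4.4 | 1.9–3.7% | 5.0% |

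The low end of each gain is the 90/10 split. At an odds ratio of 5 the other three splits give 2.1 to 2.5 points. The 4.4% at an odds ratio of 1 reflects discreteness, not stratification.

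**Step 4. Stratum effect in group A only.** With a 70/30 split balanced by arm (31 and 13 of 44), unstratified against stratified power is 86.7% and 86.9% at an odds ratio of 3, 86.9% and 87.3% at 5, and 87.0% and 87.7% at 8. The gain is 0.2, 0.4 and 0.7 points.

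**The case against.** The strongest objection is that the article never calls the primary analysis unstratified. It condenses a fuller protocol, and an analysis plan may exist; either could say that Z and V are summed over strata. That stands as a limit on certainty: a reader might infer a definite decision to ignore the strata, and the document does not show one. It does not remove the point, because the article describes the primary analysis in some detail, names covariates for the analysis beside it, and leaves out the allocation factor from both. Part of that argument is weak, though. The second analysis adjusts for imbalance, and a factor balanced by design is not an obvious candidate for such a list.

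A second objection is that no prognostic effect is claimed. The stated reason concerns whether the second step in group A can be done, and group B has laparotomy whatever the drain route. That suggests an effect of the stratum in group A more than a common effect in both arms. This also stands, and Step 4 shows how small the gain then is.

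Third, conservatism is not automatic. With a null risk of 30.5% and strata balanced by arm, the unstratified test has a size of 5.3% at a stratum odds ratio of 1, 5.0% at 2 and 4.5% at 3, so it is clearly below 5% only from about 3. In that setting the stratified test runs slightly above 5% (5.1 to 5.3%), so a small part of its gain there is extra size.

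Finally, a reader might infer that stratifying the allocation is wasted. It is not: it balances the arms on whether the second step is possible, which serves the main comparison and the planned subgroup analysis.

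**Conclusion.** The point holds as a minor one. Allocation and the described primary analysis do not match, and matching them costs almost nothing. At a stratum odds ratio of 1 the stratified test loses nothing. If the stratum is prognostic in both arms, it gains about 1 point of power at an odds ratio of 3 and mostly 2 to 2.5 points at 5 (1.2 with a 90/10 split), and keeps the size near 5%. If the stratum acts in group A only, the gain is under 1 point.

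A reader might infer that the trial is underpowered or its test invalid. Neither follows. Unstratified power is at least 85.7% in every setting tried, above the stated 80%, and where the stratum is prognostic the error is towards caution.

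The figures rest on assumed stratum splits, odds ratios, 1:1 allocation and block size. They are for a fixed test at 88 patients. The continuous boundaries, and stopping at the 52–77 patients that the article expects, were not simulated.

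**What to change.** State in the analysis section that Z and V are computed within each drain-feasibility stratum and summed before being plotted against the PEST boundaries, and that the common odds ratio across strata is reported. Use the stratum recorded at randomisation, not a later judgement on whether VARD is possible. Fix this before the first look, because the statistic is recalculated at every endpoint and the choice should not be open once data accumulate. A stratum with patients in only one arm contributes zero to both Z and V, so early looks cause no difficulty.

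The cost is one sentence, plus carrying the stratum, which the randomisation module must already hold, in the dataset sent to the biostatistician. If the full protocol or analysis plan already specifies this, a short mention in the article is enough.

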### Ethics

This study is conducted in accordance with the principles of the Declaration of Helsinki and 'good clinical practice' guidelines. The independent medical ethics committees of all 20 participating hospitals have approved the study protocol. Prior to randomisation, written informed consent will be obtained from all patients (alternatively consent by proxy will be obtained for patients who are unable to give consent, e.g., intubated patients).

### Safety and quality control

The indication and timing of intervention in necrotizing pancreatitis can be difficult. Therefore, prior to randomisation using CECT images and a 'summarized case report' an expert panel consisting of three surgeons ([name], [name], [name]), a gastroenterologist (RT) and three radiologists ([name], [name], [name]) will assess the indication and feasibility of surgical, gastroenterological or radiological intervention. All procedures will be performed by experienced radiologists, gastroenterologists or gastrointestinal surgeons. All endo-/videoscopic procedures will be videotaped. In case of a planned intervention, surgeons or radiologists from (neighbouring) participating hospitals and the trial coordinator will join the procedure in order to increase experience and enhance protocol-compliance. Every four months a study group meeting will be organised in which the CECT images and the 'summarized case report' of all newly randomised patients will be discussed. An independent monitoring-committee, consisting of two surgeons, a gastroenterologist, an epidemiologist and a radiologist, will discuss (serious) adverse events and give advice to the trial steering committee.

### Statistical analysis

#### Intention-to-treat

The analysis will be performed in accordance with intention-to-treat (ITT) principle

